#### 3.1.3 Comparison of Different Antineoplastic Therapies

The BEGYN study will allow to compare patients with various antineoplastic therapies, i.e., endocrine therapy, chemotherapy, surgery, and radiotherapy. Due to the strict adherence to the national guideline, therapy concepts are to be expected representative for the German national standard.

#### 3.1.4 Immunophenotyping

The BEGYN study will yield a deep insight into the innate and adaptive immune system during the first year after diagnosis of non-metastatic breast cancer (62). Inflammatory processes are a crucial part of the physiological response to cancer cells. Simultaneously, the BEGYN study will shed light on the effects of endocrine therapy and of chemotherapy on the immune system. Moreover, it is well recognized that moderate physical activity is associated with an improved immune status whereas excessive physical activity leads to an increase susceptibility towards (viral) infections (22). Interestingly, natural killer (NK) cells play a key role in sports physiology and in restricting tumor growth (64). Thus, the BEGYN study will be among the first studies to quantify four distinct subsets of NK cells in relation not only to breast cancer and antineoplastic therapy, but also in relation to the extent and type of physical activity.

The BEGYN study also has some limitations, such as the single center approach. However, the data will serve as a basis for designing future multicenter studies. In example, the results of the BEGYN study might help focusing the highly detailed immunophenotyping regarding the characterization of leukocyte subsets, mRNA transcripts and cytokines to the most promising variables in future study protocols. One further limitation of the study is that the quality of self-assessments may underlie intra-individual and inter-individual variations when filling out the self-assessment diary (e.g. daily documentation of physical activities, weekly read outs of the measurements of the fitness tracker etc.). Due to the need of serial measurements of the body composition, ethical concerns on X-ray exposure were the reason to use bioimpedance analysis and plicometry rather than Dual-energy X-ray absorptiometry, which is regarded as the gold standard (106). With regard to the known limitations of bioimpedance analysis and plicometry, we will compare the intra-individual relative changes over time instead of absolute values (107). In addition, we will further extend the data by estimating the body composition from the routine CT scans of the study patients (56). The BEGYN study is an observational study, thus potential causal relationships must be interpreted carefully. Ethical concerns would not allow randomizing patients into a group that would not be encouraged to exercise since this would conflict with the high evidence guidelines. However, the BEGYN study might help defining valid methods of continuous registration of physical activity for future studies to compare the role of various types of exercise, e.g., training of strength versus endurance.

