## 1 Introduction

Historic recommendations to avoid physical activity during cancer treatment to save all energy for fighting the disease have proven wrong (1–6). Breast cancer is the most common cancer in women, accounting for more than 680.000 deaths per year worldwide (7). Although modern breast cancer treatment such as improved diagnostic and staging procedures, advanced systemic therapy, surgery and radiotherapy increases long-term survival and clinical outcome of breast cancer patients, there is still a deficiency of supportive and psychosocial care (8). Breast cancer survivors are at risk of suffering potentially disabling physical and psychological sequelae, such as lymphedema, axillary web syndrome, chronic pain, osteoporosis and fractures, arthralgia, chronic fatigue syndrome and depression (9). During and after antineoplastic therapy, rehabilitation and complementary therapies are crucial to improve the quality of life and overall prognosis of breast cancer survivors (10–12).

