Multiple studies in cancer patients have demonstrated that physical activity and exercise correlate with an improved outcome regarding the course of the underlying disease and with a better tolerance to the antineoplastic treatments (13). For example, exercise had positive effects on the fatigue syndrome and quality of life in cancer (12, 14), the course of lymphedema (13, 15) and osteoporosis in breast cancer (16) and prostate cancer (17). Moreover, physical activity influences various functions of the immune system, such as the proportions of circulating leukocyte subsets and the expression of cytokines (4, 18–21). Moderate sporting activity has an immune-protective effect, whereas excessive sporting activity is associated with an increased susceptibility to infections - possibly mediated by a reduction in circulating natural killer cells (22). Natural killer cells and other leukocyte subsets play a crucial role in the physiological attempts of the organism to control cancer cells (23). Thus, Ashcraft et al. put forth the hypothesis that exercise-induced modulations of the immune status do not only alter the susceptibility to infections, but also the immune response to neoplastic diseases and the effectivity of antineoplastic therapies (24). Current data suggest that a complex interplay of the above-mentioned factors contributes to a positive correlation between the quantity of physical activities and event-free survival in cancer patients (69% reduced hazard of mortality among highly active patients) (25). In consequence, more prospective studies were recommended to characterize the influence of sporting activities on the immune system and on potential individualized rehabilitation approaches in cancer patients (9, 26, 27).

According to Mehnert et al. (28) the prevalence of any mental disorder among the major tumor entities is 32% and breast cancer has the highest prevalence of mental disorders with 42%. 17% of breast cancer patients are afflicted with anxiety disorders and 9% with affective disorders. Physical activity can affect anxiety and depression in breast cancer patients. Interestingly, leisure time physical activity was negatively related to depression, whereas occupational physical activity related positively to anxiety (29).

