## 2 Materials and Methods

### 2.1 Study Population

The BEGYN study will assess 110 female patients with non-metastatic invasive breast cancer prior to the initiation of antineoplastic therapy. The patients will be followed for one year after diagnosis. Since the study focuses on variables that are heavily influenced by gender (e.g., physical fitness and body composition), we did not include male breast cancer patients. Inclusion and exclusion criteria ensure that patients can undergo spiroergometry, blood tests, assessment of physical activities and psychological parameters during the first year after the diagnosis of breast cancer. The detailed inclusion criteria and exclusion criteria are given in **Table 1**.

**Table 1 T1:** Inclusion criteria and exclusion criteria of the BEGYN study.

Inclusion criteria	Exclusion criteria
Female sex Age ≥ 18 years Invasive, non-metastatic breast cancer Sufficient language skills to fill the questionnaires and to write an activity diary Sufficient technical skills or support for using a smart phone and fitness tracker Given written informed consent	Any antineoplastic treatment or invasive procedures (e.g., surgery for venous port) prior to baseline measurement Life expectancy < 12 months Non-invasive disease (e.g., carcinoma *in situ*) Previous or current history of other neoplasia Inability to perform a spiroergometry on a tread mill Pregnant or nursing women

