### 2.3 Clinical Assessment

Routine assessment during quarterly follow-up visits includes an anamnesis focused on potential side effects of antineoplastic therapies, measuring the body weight and blood pressure.

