### 2.5 Body Composition

#### 2.5.1. Bioelectrical Impedance Analysis

The body composition will be determined based on bioelectrical impedance analysis (BIA) (TANITA scale™, Tanita Europe BV, Stuttgart). The test person stands barefoot on a body scale and holds sensors in both hands. Using the impedance between the four measuring points, numerous data can be collected that provide information on the muscle, fat, bone and water content of the whole body and individual compartments. Bioimpedance analysis is routinely used in the context of nutritional advice and sports medicine, but it can also shed light into disease processes, such as hemodialysis patients (55) (**Table 4**). When accessible, the body composition will also be estimated by using routine CT scans of the study patients as previously published (56).

**Table 4 T4:** Measurements by scale and bioimpedance analysis.

Item	Unit
Weight	kg
Total body fat	%
Total muscle mass	kg
Bone mass	kg
Body-Mass-Index	Kg/m²
Basal metabolic rate	kcal
Metabolic age	years
Total body water	%
Visceral fat	kg
Segmental muscle mass in arms, legs, and torso	kg
Segmental body fat in arms, legs, and torso	%

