#### 2.5.2 Plicometry (Calipometry)

Plicometry allows a standardized estimate of the body fat status which can change under influences such as sport, chemotherapy or cancer (57–60). In the BEGYN study, fat distribution is assessed using the skinfold measurement using the 3 point-method (triceps, suprailiac skinfold, and thigh) according to Jackson and Pollock (61). (**Figure 2**). The total body subcutaneous fat tissue (in kg) was estimated from the plicometry measurements using the formula (61):

$$\text{Total}\;\text{body}\;\mathrm{subcutaneous}\;\text{fat}\;(\text{kg})\;=\;[(4.95/(1.0994921-(0.0009929^{*}\text{S})+(0.0000023^{*}{\text{S}}^{2})-(0.0001392^{*}\text{age}\{\text{in years}\})))-4.5{]}^{*}100.$$

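### Within-patient change does not remove arm swelling that begins after baseline, and no rule in the text protects the arm bioimpedance and triceps data from it

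*Protocol article*

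**What the plan says.** Table 1 (section 2.1) excludes patients with "Any antineoplastic treatment or invasive procedures (e.g., surgery for venous port) prior to baseline measurement". Baseline is therefore before surgery for every participant, and quarterly visits follow.

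Body composition is measured in two ways. For bioimpedance, section 2.5.1 states: "Using the impedance between the four measuring points, numerous data can be collected that provide information on the muscle, fat, bone and water content". The patient stands barefoot and holds a sensor in each hand. Table 4 lists segmental muscle and fat for arms, legs and torso, and one water value for the whole body. For skinfolds, section 2.5.2 uses three sites, one of which is the triceps. The text names no side; Figure 2, which is not shown, may do so.

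The protocol's answer to the weaknesses of these methods is in the limitations paragraph at the end of section 3.1.4: "With regard to the known limitations of bioimpedance analysis and plicometry, we will compare the intra-individual relative changes over time instead of absolute values". The next sentence adds body composition from routine CT, which section 2.5.1 limits to scans that are accessible.

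For the arm itself, section 2.3 describes follow-up visits with "an anamnesis focused on potential side effects of antineoplastic therapies, measuring the body weight and blood pressure". The diary records symptoms (section 2.4.1), and the QLQ-BR23 covers arm and breast symptoms (Table 8). The text lists no arm circumference, volume or grading. The Introduction names lymphedema among the sequelae and says that exercise affects its course.

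**The concern.** Comparing a patient with herself removes an error that she carries unchanged through all visits. Swelling of the arm after breast or axillary surgery is not such an error: it is absent at baseline and may appear, grow or recede later. If the scale reads the fluid as muscle or fat, or the swollen arm gives a thicker triceps fold, the within-patient change contains the artefact in full. Removal of breast tissue could affect the torso segment in a similar way.

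This matters because the Introduction presents bioimpedance as the way to detect loss of muscle and gain of fat. Section 3.1.3 plans comparisons between therapies, including surgery and radiotherapy, so the error may differ between the groups compared. Since the Introduction also ties exercise to the course of lymphedema, the error may be related to activity as well. The subgroup analyses and propensity-score matching in section 2.9 address confounding; they do not correct a mismeasured outcome.

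**Working it through.** **1. What within-patient change removes.** Write the measured value at visit t as M(t) = T(t) + e(t), where T is the true value and e the error. The change from baseline is M(t) − M(0) = [T(t) − T(0)] + [e(t) − e(0)]. If e is constant, the last bracket is zero. In the same way, a constant multiplicative error cancels from the relative change M(t)/M(0). Table 1 places baseline before surgery, so for treatment-related swelling e(0) = 0 and e(t) = s. The bracket equals s, and nothing cancels. This step needs no outside figure.

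**2. Illustration for arm muscle.** The documents give no device error, arm mass or incidence. Assumed values:
- muscle in one arm 2.0 kg, with no true change;
- swelling of 200 to 500 ml (1 ml taken as 1 g), half to all of it read as muscle;
- 5% to 30% of patients affected.

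Fluid read as muscle: 0.2 × 0.5 = 0.1 kg, up to 0.5 × 1.0 = 0.5 kg.

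| Quantity | Low | High |
|---|---|---|
| Affected arm, relative change | 0.1/2.0 = 5% | 0.5/2.0 = 25% |
| Both arms stored as one value (4.0 kg) | 0.1/4.0 = 2.5% | 0.5/4.0 = 12.5% |
| Patients affected, of 110 | 0.05 × 110 = 5.5 | 0.30 × 110 = 33 |
| Cohort mean, one-arm measure | 0.05 × 5% = 0.25% | 0.30 × 25% = 7.5% |
| Cohort mean, kg | 0.05 × 0.1 = 0.005 | 0.30 × 0.5 = 0.15 |
| Same, against an assumed 40 kg total muscle | 0.0125% | 0.375% |

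The cohort rows assume that the measure always includes the affected arm.

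**3. Illustration for the skinfold.** The formula printed in section 2.5.2 is F = [4.95/D − 4.5] × 100, with D = 1.0994921 − 0.0009929·S + 0.0000023·S² − 0.0001392·age. Assume age 55 and S = 80 mm. Then D = 1.0271241 and F = 31.93. Only the triceps reading is raised:

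| Added at triceps | F | Difference | Relative |
|---|---|---|---|
| 3 mm | 32.80 | +0.87 | +2.7% |
| 5 mm | 33.37 | +1.44 | +4.5% |
| 8 mm | 34.22 | +2.29 | +7.2% |

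At S = 70 mm, a reading 5 mm higher gives +1.53 (+5.3%), so the result depends only moderately on the assumed S.

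**4. Whether other collected data fill the gap.** QLQ-BR23 arm symptoms, the side-effect history and the diary can flag affected patients, but they do not measure volume. Total body water cannot locate fluid in one arm. CT does not depend on arm impedance or the triceps fold, but exists only for some patients. No sentence in the article connects any of the arm information to the body-composition analysis.

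**The case against.** The strongest reply has four parts.

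First, a reader might infer that lymphedema is not measured and will go unreported. The documents do not support that. The QLQ-BR23 covers arm symptoms, follow-up visits take a side-effect history, and the diary records symptoms. Only an objective arm measure is missing from the text, and even there Figure 1 and the full protocol are not shown. The Introduction names lymphedema as background, not as a study aim.

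Second, a reader might infer that the association between activity and body composition is biased in a known direction. The documents do not say how this scale treats fluid, how often swelling occurs, or whether affected patients are less active. The sizes above are assumptions. On those same assumptions the whole-body effect is below 0.4% on average.

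Third, within-patient change is not the only remedy. CT is a second one, though partial, and the paragraph does not claim that every error is removed.

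Fourth, the analyses are exploratory (section 2.9), and body composition is one of many domains.

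All four stand, and they limit the weight of the point. They leave its core intact: the article names a specific remedy, and that remedy cannot work for an error that starts after baseline. A fuller protocol could add a safeguard, but it could not make within-patient change remove new swelling.

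**Conclusion.** The point holds in a limited form. Given a baseline before surgery, treatment-related arm swelling is a new, time-varying error. Relative change leaves it in the arm segments and the triceps fold, and the article does not say how the available arm-symptom data will be used to guard against it. That conclusion follows from the text alone.

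The size and direction do not. Under the stated assumptions, the error is 5% to 25% in an affected arm, 0.25% to 7.5% on average over the cohort for a one-arm measure, and 2.7% to 7.2% in an affected patient's skinfold result. Whole-body muscle would hardly move. The arm segments and the skinfold result are therefore the outcomes to protect. Severity: consider.

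**What to change.** Make the change at the analysis stage. Recruitment closed in January 2021 and data collection was due to end in March 2022 (section 3.3).

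- Take the operated side and the type of breast and axillary surgery from the treatment record.
- Use the leg segments as the main segmental muscle measure. Use the non-operated arm only if left and right values are stored separately. Table 4 does not say that they are, so check this first.
- Repeat the arm, torso, whole-body and skinfold analyses without patients flagged by QLQ-BR23 arm symptoms, recorded swelling or mastectomy.
- Use available CT as a cross-check.
- Keep the skinfold side unchanged and record which side was used. Switching sides within a series would break the within-patient comparison.
- State in the limitations paragraph that within-patient change does not correct for swelling or tissue removal after surgery.

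The cost is a short extraction from surgical records, some additional sensitivity analyses and a sentence of text. The drawback is that these analyses rest on fewer patients or segments. Patients operated on both sides would contribute leg values only to the main segmental analysis.

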### 3.2 Conclusion

The holistic approach over 12 months including physiological, psychological, and immunological data is the main strength of the BEGYN study. By including a homogeneous group of 110 female non-metastatic breast cancer patients, the study will provide highly valid data on the complex interplay between physical activity, underlying disease, type of therapy and psychological parameters.

The BEGYN study provides a uniquely thorough analysis of non-metastatic breast cancer patient during the first year after diagnosis.

### 3.3 Ethics and Dissemination

The study is carried out at the Department for Gynecology, Saarland University Medical Center and has been approved by the ethics committee of the Medical Association of Saarland (study # 229/18). Written consent is obtained from the patient in accordance with the Declaration of Helsinki. Any amendment to the protocol will require the formal modification and approval by the same local ethics committee that approved the study prior to implementation and will be described transparently in subsequent reports. This study is registered at German Clinical Trials Register (DRKS) (DRKS00024829). Patient recruitment took place between September 2019 and January 2021 and data collection will continue until March 2022.

## Ethics Statement

The studies involving human participants were reviewed and approved by ethics committee of the Medical Association of Saarland (study # 229/18). The patients/participants provided their written informed consent to participate in this study.

